### Participants

A total of 30 pediatric patients will be recruited from the Institut St Pierre, France. The inclusion criteria for this study will be adolescents aged from 11 up to 18 years with a diagnosed spastic diplegia cerebral palsy, patients with walking abilities (Gross Motor Function Classification System levels I to III), the ability to activate knee flexors and extensors voluntarily, and cognitive abilities to understand the instructions. The exclusion criteria for this study will be cardiovascular disorders; fractures of any type; history of hip subluxation, dislocation, or important scoliosis (>40° of curvature); surgery of the lower limb within the last year; botulinum toxin injection within the last 3 months; significant contracture of the knee flexors and extensors (less than 90° of knee active range of motion [ROM]); and insufficient understanding of the French language. All the participants and their legal tutor will be informed of the study procedures in agreement with the ethical standards of the Helsinki Declaration and will sign an informed consent.

### Intensive Rehabilitation

The intensive rehabilitation will be conducted over a 3-week period. All participants will follow the intensive rehabilitation. Physiotherapy will be performed twice a day. Hydrotherapy and virtual reality gait training will be performed on a daily basis. During the 3 weeks of rehabilitation, the IG and CG will practice for a total of 59 and 52 hours, respectively. The hourly repartition can be found in Figure 1.

Physiotherapy sessions are expected to last for 60 minutes and will include lower limb stretching exercises and strengthening of the lower extremities (Table 1). All exercises realized during a typical physiotherapy session are described in Table 2. Hydrotherapy sessions will last for 60 minutes and will include stretching exercises, aerobic exercises, and strengthening of the lower extremities (Table 3). Hydrotherapy exercises are realized with water up to the patient’s belly. All exercises realized during a typical hydrotherapy session are described in Table 2. The virtual reality gait training will last for 30 minutes in total and will focus on improving different gait parameters with video games. Another aim of the virtual reality training will be to perform balance exercises. Perturbations will be added to challenge participants. All exercises realized during a Gait Real-time Analysis Interactive Lab (GRAIL) session are described in Table 2. The same video games will be performed for every adolescent (Table 4). A summary of all exercises performed during the intensive rehabilitation is presented in Figure 2.

**Figure 1 figure1:**
[figure not shown]
Rehabilitation program with the total amount of training. During the 3 weeks of rehabilitation, the isokinetic training group and control group will respectively perform a total of 48 hours and 41 hours of active training. *Only performed by the isokinetic training group. GRAIL: Gait Real-time Analysis Interactive Lab; GT: gait training; ST: strength training.

**Table 1 table1:** Characteristics and rehabilitation volume for the physiotherapy sessions.

Interventions and exercises		Sets, n	Repetitions (seconds), n	Contraction types
**Stretching**				
	Triceps surae	2	20	N/A^a^
	Quadriceps	2	20	N/A
	Hamstrings	2	20	N/A
	Iliopsoas	2	20	N/A
**Strengthening**				
	Foot plantar flexion with elastic band	6	10	CON^b^ and ECC^c^
	Foot dorsiflexion with elastic band	6	10	CON and ECC
	Sit to stand	6	10	CON and ECC
	Knee flexion with elastic band	6	10	CON and ECC

^a^N/A: not applicable.

^b^CON: concentric realized as fast as possible.

^c^ECC: eccentric maintained for 2-3 seconds.

**Table 2 table2:** Description of intensive rehabilitation sessions performed by adolescent in both groups.

Interventions and exercises				Description		Resistance added
**Physiotherapy**						
	**Stretching**					
		Triceps surae	Patient in supine position. PT^a^ is pushing the patient foot in dorsiflexion with the knee extended as much as possible		N/A^b^	
		Quadriceps	Patient in prone position. PT is bending the patient knee and maintaining the patient hip against the table		N/A	
		Hamstrings	Patient in supine position. PT is maintaining the patient knee extended and adding as much hip flexion as possible. The opposite leg must stay extended on the table		N/A	
		Iliopsoas	Patient in supine position on the lower part of the table. PT is maintaining a hip extension with a knee flexion. The opposite leg is placed on the chest of the PT		N/A	
	**Strengthening**					
		Foot plantar flexion	Patient in supine position with knee extended. Ankle placed in dorsiflexion. Elastic band placed around the ball of the foot and help by the patient		Resistance band of various resistances	
		Foot dorsiflexion	Patient in supine position with knee extended. Ankle placed in plantar flexion. Elastic band placed around the instep of the foot and held by the PT		Resistance band of various resistances	
		Sit to stand	Patient seating on a chair and push with his feet on the ground to stand		Dumbbells from 5 kg to 10 kg	
		Knee flexion	Patient in prone position with knee extended. Elastic band is placed around patient ankle and held by the PT		Resistance band of various resistances	
**Hydrotherapy**						
	**Stretching**					
		Triceps surae	Patient standing against the pool. One lower limb in front of the other. Both feet on the ground with the back foot in maximal dorsiflexion		N/A	
		Quadriceps	Patient standing against the pool. Holding one lower limb and bending toward knee flexion while the other hand is stabilizing against the pool.		N/A	
		Iliopsoas	Patient kneeling against the pool. One knee against the ground and the other one bended. Pushing his gravity center forward		N/A	
	**Strengthening**					
		Forward walking	Patient standing and walking forward at high intensity inside the swimming pool with water up to the belly.		Resistance band	
		Backward walking	Patient standing and walking backward at high intensity inside the swimming pool with water up to the belly.		Resistance band	
		Side walking	Patient standing and walking from side to side at high intensity inside the swimming pool with water up to the belly		Resistance band	
		Calf raises	Patient standing against the pool with water up to the belly. Pushing against the ground toward maximal plantar flexion and going back to the ground slowly		Water resistant weight	
		Squat	Patient standing against the pool with water up to the belly. Squatting up to 90 degrees of knee flexion and back to the initial position		Water resistant weight	
**GRAIL^c^**						
	**Gait training**					
		Rope bridge	Patient standing on a treadmill. 4 markers are placed on posterior and anterior superior iliac spine. A self-paced mode is used to let the patient walk at a comfortable speed		Sway: level 1 to 3; pitch: level 1 to 3; encounters: level 1 to 3	
		Step on it	Patient standing on a treadmill. 2 markers are placed on both lateral malleoli. Treadmill speed is set based on gait analysis assessment.		Increasing step length and decreasing step width	
	**Balance**					
		Perturb	Patient is standing on the treadmill. Anteroposterior and mediolateral stimuli are produced from the treadmill.		Automatic mode starting from level 1 to 5	

^a^PT: physiotherapist.

^b^N/A: not applicable.

^c^GRAIL: Gait Real-time Analysis Interactive Lab.

**Table 3 table3:** Characteristics and rehabilitation volume for the hydrotherapy sessions.

Interventions and exercises			Sets, n		Repetitions (seconds), n		Contraction types
**Stretching**							
	Triceps surae	2		20		N/A^a^	
	Quadriceps	2		20		N/A	
	Iliopsoas	2		20		N/A	
**Strengthening**							
	Walking forward	6		30		N/A	
	Walking backward	6		30		N/A	
	Side walking	6		30		N/A	
	Calf raises	5		10		CON^b^ and ECC^c^	
	Squats	5		10		CON and ECC	

^a^N/A: not applicable.

^b^CON: concentric realized as fast as possible.

^c^ECC: eccentric maintained for 2-3 seconds.

**Table 4 table4:** Characteristics and rehabilitation volume for the Gait Real-time Analysis Interactive Lab sessions.

Exercises	Aim	Sets, n	Duration (minutes^a^), n	Parameters
Rope bridge	Walk on treadmill with perturbations	4	2	Sway, pitch, and encounters
Perturb	Stand on the treadmill with perturbation to improve balance	4	2	Automatic mode
Step on it	Walk on the treadmill with targets to hit to improve step width and length	4	2	N/A^b^

^a^Minutes for the time for each exercise; seating breaks of 1 minute are respected between each sets.

^b^N/A: not applicable.

**Figure 2 figure2:**
[figure not shown]
Images of the guidelines for the intensive rehabilitation program and the isokinetic strength training program. Both groups will follow the exact same intensive rehabilitation program. Only the isokinetic training group will follow the isokinetic strength training program. *Knee flexors and extensors are trained at various speeds in concentric and eccentric modes with different intensities depending on the training week.

### Isokinetic Training Intervention

The IG will also receive a total of 9 supervised isokinetic training sessions over 3 weeks based on given guidelines for isokinetic training [29-31]. Adolescents will train between 70% and 80% of the maximal value in Newton-meter reached during the test at the different speeds (Table 5). A visual feedback will be displayed to the participants, with a frame range showing the target strength to reach for every set. A rest time of at least 24 hours between sessions will be observed for every participant. Based on MacArdle et al’s [13] findings, 1 single training session will consist of 3 sets of 5 repetitions at a speed of 30 degrees/s concentrically, 3 sets of 8 repetitions at 120 degrees/s concentrically, and 3 sets of 3 repetitions at 30 degrees/s eccentrically. Therefore, strength, hypertrophy, and power will be performed. One repetition consisted of a complete knee extension and flexion, based on the ROM reached during the first assessment. A 90-second rest will be respected between each set. Every session will be preceded by a 5-minute warm-up and followed by a 5-minute cooldown. All exercises realized during isokinetic sessions are shown in Figure 2. One session is expected to last for approximately 45 minutes [29,30,32]. A summary of the exercises performed in the isokinetic strengthening program is presented in Figure 2.

**Table 5 table5:** Isokinetic strengthening program for the intervention group.

Weeks	Sets, n	Intensity, %^a^	Contraction type
1 and 2	3	70	CON^b^ and ECC^c^
3 and 4	3	75	CON and ECC
5 and 6	3	80	CON and ECC

^a^Percentage from maximal reached value at each speed.

^b^CON: concentric.

^c^ECC: eccentric.

### Primary Outcomes

#### Strength

Muscle strength will be assessed with an isokinetic dynamometer (CON-TREX, MJ Multijoint module, Medimex, CMV AG). Patients will be installed as described previously. Patients will perform an aerobic warm-up for 5 minutes and stretching of the quadriceps and hamstring prior to the test. The ROM will be set based on the extension abilities of the patients. Knee flexors and extensors will be assessed in a concentric mode for 3 repetitions at a speed of 30 degrees/s, 5 repetitions at a speed of 120 degrees/s, and for 8 repetitions at a speed of 180 degrees/s; in an isometric mode at 45° of knee flexion for 5 seconds; and in an eccentric mode for 3 repetitions at a speed of 30 degrees/s. The isokinetic equipment is shown in Figure 2.

Between the 2 concentric, the isometric, and the eccentric tests, 90 seconds of recovery will be allowed. Verbal encouragement will be provided for all participants during the entire test. The highest value in Newton-meter, the maximum reached speed in degrees/s, and the total work produced in joules will be considered for data analysis.

A recent meta-analysis from Muñoz-Bermejo et al [6] showed good to excellent levels of reliability of isokinetic dynamometer in measuring knee extensors and knee flexors strength in children with cerebral palsy, with an interclass correlation coefficient (ICC) ranging from 0.7 to 1 in the dominant and the nondominant lower limb.

#### Gait Assessment

Patients will perform a walking test on the GRAIL (Motekforce Link). The GRAIL technology consisted of a split-belt treadmill with integrated force plates, an incurved virtual reality screen, and a 3D motion capture system (VICON). The treadmill is built with a self-paced mode, allowing patients to walk at a comfortable speed during the entire test.

Spatiotemporal parameters such as gait speed, stride length, step width, and stance time will be recorded during the walking test. Gait speed (m/s) is defined as the average speed recorded during the entire test after removing the first and last seconds to undo the acceleration and deceleration phenomena. Stride length (cm) is defined as the average anteroposterior distance between heel strikes of the same lower limb. Step width (cm) is defined as the average mediolateral distance between both feet. Stance time (s) is defined as the time between heel strike and toe-off from the same lower limb.

Kinematics data will also be collected through the 3D motion capture system. A total of 22 markers will be placed on patients’ lower limbs following the human body model, which has been described as a valid method to measure kinematics [33]. Hip, knee, and ankle ROM will be captured during the entire gait assessment in the sagittal, transversal, and horizontal planes. Electromyography activity will be recorded for both lower limbs using surface electrodes on 2 important muscles. The rectus femoris and biceps femoris will be recorded. These 2 muscles are important for knee function, including extension and flexion.

A 6-minute walking test (6MWT) will also be performed on the GRAIL. The treadmill will be set to the self-paced mode. Patients will be asked to walk during the entire test. The total distance reached during the test will be registered for data analysis. Performing the 6MWT on the GRAIL technology has shown good construct validity and reproducibility [34,35]. The Borg scale will also be measured before and after the 6MWT for every patient as an indicator of the level of exertion perceived during the test [34,35].

### Secondary Outcomes

#### Spasticity

Spasticity within knee flexors and extensors will be assessed with an isokinetic dynamometer (CON-TREX, MJ Multijoint module, Medimex, CMV AG) by applying a passive movement at a speed of 180 degrees/s to stretch the muscles. Patients will be installed on the isokinetic seat with 80° of hip flexion, 90° of knee flexion, and no restriction within the ankle joint. The mechanical axis of the dynamometer will be aligned with the lateral epicondyle of the femur. The tibial pad will be placed 3 cm above the lateral malleolus. The trunk and the thigh of the patients will be stabilized with belts. Both limbs will be assessed for 10 consecutive times from 90° to 25° of knee flexion and back to 90°. A 60-second rest break will be respected between each movement. The patient will receive the instruction to rest as much as possible during the entire movement. Prior to the spasticity test, a filter for gravity correction will be applied based on the patient’s limb weight. The isokinetic dynamometer will record the forces, angles, and speed during the entire movement. The first and last 5° of each movement will be excluded from the data analysis to avoid errors from the effect of inertia [24]. The test will be interrupted if the force, in Newton, applied to the dynamometer is greater than half the patient’s body weight. Patients will be instructed to stop the test if they feel any pain or are scared [36].

The peak resistive torque will be calculated at baseline and after a 3-week intensive training program within both groups. In the knee, the peak resistive torque has shown good relative reliability at a speed of 180 degrees/s, with an ICC of 0.86 for knee extensor peak torque and an ICC of 0.80 for knee flexor peak torque [36].

#### Knee Joint Position Sense

Knee JPS will be assessed with an isokinetic dynamometer (CON-TREX, MJ Multijoint module, Medimex, CMV AG). Patients will be installed as described previously. The patient’s resting position will be set to a preselected joint angle of 45° of knee flexion. Knee JPS will consist of the position-reposition angle difference of the dominant leg. The angular speed for the repositioning task will be set at 2° per seconds as described by El Shemy [37]. Prior to the test, every adolescent will participate in a practice session to become familiar with the task. For the test, the patient’s limb will first be placed at a knee angle of 45° for 10 seconds, and then the lower limb will go back to 90° of knee flexion. Finally, the dynamometer will move the lower limb through extension at the same speed. Once patients feel that they have reached the target position again, they will press the button and stop the test. Patients will be blindfolded, and the test will be performed in quiet surroundings to eliminate visual and auditory stimuli. The test will be performed 3 consecutive times, and the mean will be calculated for data analysis.

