### Objectives

The primary aim of this randomized controlled trial is to compare the effect of intensive rehabilitation combined with an isokinetic progressive strengthening program to intensive rehabilitation alone on gait parameters and muscle strength in patients with cerebral palsy. Another goal of this study is to determine whether adding an isokinetic program is more effective than just intensive rehabilitation in decreasing spasticity and improving joint position sense in patients with cerebral palsy.

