### Sample Size

Sample size calculation was realized using G*POWER statistical programming (version 3.1.9.2; Franz Faul): power (1−α error *P*)=.85, α=.05, effect size=1.1, with a 2-tailed for a comparison of 2 independent groups. This calculation was based on the results of a pilot study based on ratio improvement following 2 specific interventions in patients with cerebral palsy. It will take 15 participants in each group to complete this study.

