### Data Analysis

Descriptive statistics will be used to describe gender, age, and Gross Motor Function Classification System. Primary and secondary outcomes will be analyzed in the same way. The assumption of normality will be checked by visual inspection of the q-q plot and the box plot of the data within groups. A Shapiro-Wilks test will also be performed on the data within groups. The homogeneity of variance will be checked using Levene test.

If the data are normally distributed, an independent *t* test will be carried out for each variable to see if there are differences between the experimental and control groups. The 95% CI for the mean differences will be determined. Pearson *r* will be used to calculate the effect size.

If the data are not normally distributed, a Wilcoxon rank-sum test will be used for each variable to determine if there are any significant differences between groups. Pearson *r* will be calculated as a measure of effect size.

The data analysis will be performed using SPSS (25.00, IBM Corp). For the data analysis, the researchers will use a 95% CI, considering all those variables with a *P* value of less than .05 to be statistically significant.

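### Knee joint position sense is scored as a mean angle difference not stated to be absolute; if signed, over- and undershoots cancel and a gain in accuracy can be missed

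*Protocol article*

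**What the plan says.** Knee joint position sense is one of two secondary outcomes in the protocol article. Its section gives a scoring rule in two parts: "Knee JPS will consist of the position-reposition angle difference of the dominant leg", and "The test will be performed 3 consecutive times, and the mean will be calculated for data analysis". The limb is shown 45° of knee flexion and returned to 90°. The dynamometer then moves it towards extension at 2° per second: "Once patients feel that they have reached the target position again, they will press the button and stop the test". The section cites a published study for that speed, not for the scoring. No sign convention is given, and nothing says that the size of the error is meant.

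The Objectives section asks whether the added programme is "more effective than just intensive rehabilitation in decreasing spasticity and improving joint position sense". Under Data Analysis, "Primary and secondary outcomes will be analyzed in the same way", and for normally distributed data "an independent *t* test will be carried out for each variable to see if there are differences between the experimental and control groups"; otherwise a Wilcoxon rank-sum test is used. That section does not settle the sign either.

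**The concern.** The stated aim is better joint position sense, which means reproduced angles closer to 45°. A difference between two angles, read literally, carries a sign, and the mean of three signed differences measures directional bias rather than accuracy. The child stops a moving limb, so a stop on either side of the target is possible and the errors can cancel.

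Two things are at stake if the signed reading is used. A child who becomes more consistent without shifting direction shows no change. And the scale has no better or worse end: a move from +8° to +2° is a change of −6°, a move from −8° to −2° is a change of +6°, and both are the same improvement. A test of group means adds them to zero.

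**Working it through.** **The plan's own figure.** The article states no mean, SD or power for this outcome. Its only computed figure is the sample size: "α=.05, effect size=1.1", power 0.85, two-sided, giving 15 per group. The normal approximation gives 15 (power 0.854). The exact noncentral t gives 0.828 at 15 and needs 16. The present point uses only the 15 per arm and does not depend on this small gap.

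**Cancellation by hand** (three trials, degrees from target):

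| Trial errors | Signed mean | Mean absolute error |
|---|---|---|
| +6, −6, 0 | 0 | 4.0 |
| +1, −1, 0 | 0 | 0.67 |
| +6, +5, +7 | 6 | 6 |
| +2, +1, +3 | 2 | 2 |

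Rows 1 and 2 are a real gain that the signed mean does not register. Rows 3 and 4 are a gain that both scores show.

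**Model.** Error in one trial = *b* + *u* + *w*, where *b* is a directional bias common to the arm, *u* is the child's own bias (SD σ_b) and *w* is trial scatter (SD σ_w). All degree values are assumptions.

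- The signed mean of 3 has expectation *b* and variance σ_b² + σ_w²/3. If *b* is equal in both arms, the expected group difference is 0, and a test of means rejects at about α = 0.05 however much scatter shrinks. The rank-sum test is little help: two symmetric distributions with the same centre favour neither arm in rank.
- With *b* = 0, the expected absolute error is √(2/π) × √(σ_b² + σ_w²). For SDs 5 and 4 this is 0.798 × 6.403 = 5.11°. For 2.5 and 2 it is 0.798 × 3.202 = 2.55°. For 3 and 2.5 it is 0.798 × 3.905 = 3.12°.
- If *b* falls from 6° to 3° with σ_b = 2 and σ_w = 3, the SD of the signed mean is √(4 + 9/3) = 2.646. Then d = 3/2.646 = 1.134, the noncentrality is 1.134 × √(15/2) = 3.105, and power on 28 degrees of freedom is 0.85.

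**Simulation**: 20,000 trials, 15 per arm, three repetitions per child, two-sided t test at 0.05 on one post-treatment score without a covariate. SDs are given as σ_b/σ_w, control to isokinetic arm.

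| Assumed gain | Signed mean | Mean of absolutes | Absolute of mean |
|---|---|---|---|
| *b* = 0; 5/4 to 2.5/2 | 0.05 | 0.89 | 0.61 |
| *b* = 0; 5/4 to 3/2.5 | 0.05 | 0.62 | 0.38 |
| *b* = 0; 4/4 to 2/2 | 0.05 | 0.93 | 0.61 |
| *b* = 0; 2/6 to 2/3 | 0.05 | 0.89 | 0.27 |
| *b* = 3 in both; 4/4 to 2/2 | 0.05 | 0.48 | 0.20 |
| *b* 6 to 3; 2/3 in both | 0.85 | 0.80 to 0.81 | 0.83 |
| *b* 6 to 3; 4/4 to 2/2 | 0.58 to 0.59 | 0.91 to 0.92 | 0.78 |

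Ranges show the spread over repeated runs.

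**The case against.** The strongest reply is that the article never calls the difference signed and names no positive direction. The difference between two angles can equally be a magnitude, and the objective makes sense only on that reading, under which nothing cancels. This stands, so the point has to be conditional. A reader might infer that the endpoint is a signed mean and that any real gain is therefore invisible to the planned test. The article does not support that: it fixes no sign, and even on the signed scale a falling shared bias remains visible.

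A shared bias is also plausible here, because the target is always approached from the same side and a moving limb is stopped with a button. The value of 0.05 in the first rows follows directly from giving both arms the same bias. This too stands. So does the remark that halving all error is a generous effect when both arms receive the same intensive rehabilitation.

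The reply that a journal article may leave scoring detail to a fuller document stands only in part. This article did not leave scoring out. It gives the measure and the averaging, and at least three endpoints fit its words. In the first row of the simulation their power is 0.05, 0.89 and 0.61.

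Finally, baseline adjustment is a separate matter from the sign. That is correct: no power figure here relies on it.

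**Conclusion.** The scoring rule is ambiguous, and its literal reading does not measure the accuracy that the objective aims to improve. If the difference is signed, a gain confined to scatter goes undetected (power about 0.05, against 0.48 to 0.93 for the mean absolute error across the assumed cases). A combined gain in bias and scatter is detected less often (0.58 to 0.59 against 0.91 to 0.92). A gain in shared bias alone is detected slightly more often (0.85 against 0.80 to 0.81). If the difference is already meant as absolute per trial, nothing is lost and only the wording needs completing.

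All these figures rest on normal errors and assumed SDs and biases. The matter concerns one secondary outcome. It should still be settled before data are seen, because the same recordings can be scored in ways that give quite different tests.

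**What to change.** In the section on knee joint position sense, define the endpoint as the mean over the three trials of |reproduced angle − 45°|, in degrees, with the absolute value taken before averaging and lower values meaning better. Taking it after averaging recovers only part of the loss when scatter is what improves. Report the mean signed error descriptively, with its positive direction stated. Compare the groups at T1 with the T0 absolute error as covariate; the T0 measurement is already planned.

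The cost is one sentence on scoring and one on the model. The recordings, the visits and the sample size do not change, and the definition is sound whichever reading was intended.
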